##### Baseline measures of both groups

The quality of decision support skills will be assessed using audio-taped interactions between participants and simulated patients. Simulation scenarios have been created and vetted by a panel of Palliative Advanced Practice Nurses. Simulated patient callers will receive a training and feedback session facilitated by an experienced trainer prior to placing the call to participants. Simulated patient callers will contact each participant and engage in a standardized scenario expressing difficulty related to a place of end-of-life care decision. Calls will be tape recorded and quality scored using the Decision Support Analysis Tool (DSAT) [56].

##### 2. Intervention (experimental) group

Participants assigned to the intervention group will:

a. Complete an on-line decision support tutorial which introduces the 'When you need extra care decision aid', case studies and quizzes related to place of care decision support.

b. Participate in a half day skills building workshop. The workshop contains aggregated feedback on baseline simulated calls; opportunities to observe, compare and contrast a traditional patient education approach to a patient decision support approach; role play using the 'When you need extra care decision aid' and peer scoring of the quality of their decision support provision using the DSAT. A determinants of place of care knowledge module will also be delivered. At the end of the workshop, participants will complete a questionnaire eliciting perceived utility/usability of the a) workshop content, and b) decision support protocol.

c. Participate via telephone in an education outreach session to identify areas needing clarification, share problem solving in using the decision support protocol, and to obtain further feedback.

d. Complete a questionnaire eliciting satisfaction with content and process of education program.

##### 3. Post measures of both groups

a. After the auto-tutorial, knowledge tests will be administered.

b. 2–6 weeks following completion of the full intervention a TPB based survey eliciting behavioral intention to integrate decision support in practice and related attitudes, norms, and perceived control will be administered.

c. 2–6 weeks following completion of the full intervention the quality of the participants' decision support skills will be assessed with a different simulated patient scenario using the same methodology as the baseline assessment.

**Proposed Intervention **Details of the educational intervention follow.

#### Decision Support Tutorial

Developed by Ottawa Health Decision Centre, Clinical Epidemiology Unit of the Ottawa Health Research Institute (OHRI) this on-line, self-learning resource has been used to train clinicians, graduate students and undergraduate nursing students; US and BC tele-health center nurses; UK urology nurses; and nurses in family practice units in Ontario. Three modules provide 1) an overview of decisional conflict with a three step path to guide decision support, 2) case studies profiling decision support tools (including a decision support protocol) and processes with embedded quizzes to assess comprehension and provide feedback; and 3) a final integrated knowledge test. The original tutorial will be adapted to decisions about the place of terminal care. The tutorial is hosted by the University of Ottawa and is password protected. Participants will be asked to complete the auto-tutorial one week prior to the workshop.

#### Decision Support Protocol

Participants will be introduced to a decision aid in the tutorial. The decision aid guides patients in advanced planning of location of care and is entitled 'When you need extra care decision aid'. The decision aid is based on the Ottawa Decision Support Framework and the Ottawa Decision Support Practitioners Guide (OPDG). The four page decision aid provides a structured approach to assess patients' decisional needs, provide tailored decision support to address needs and evaluate patients' progress in decision making. There are five elements: 1) general information about place of care options and palliative care; 2) self report of functional and symptom status over the past week based on the Palliative Performance Scale [57] and the Edmonton Symptom Assessment Scale [58] respectively; 3) a self-ranking of which reasons for each option are considered most important; 4) an assessment of what else patients need to prepare for decision making; and 5) a summary of next steps.

Content is based on: a) systematic reviews of literature [4,59,60]; b) previous research on women's decision making needs regarding place of care at the end of life [3]; previous research on family members' decision making needs at the end of life [61] and d) the primary investigator's clinical experience in palliative care. Participants will be provided with a hard copy of the protocol as well as access to the online version.

#### Skill building workshop

Within three weeks of the online tutorial, a half day workshop will be conducted. Content will be based on the pre-intervention TPB needs assessment and also a) practical applications of material learned in the tutorial; b) a video illustrating a clinical application of the decision aid; c) a video contrasting a traditional patient education approach and a decision support approach in a clinical scenario d) role play using the decision support protocol; e) self and peer appraisal during role play and f) discussion about barriers and facilitators to integrating decision support into clinical practice. Use of a facilitator who provides face to face communication and uses a range of enabling techniques has been shown to have some impact on changing clinical practice [62].

Specific workshop objectives are that participants will:

• understand concepts of decisional needs, decision support, and decision quality,

• learn to use decision support tools,

• evaluate decision support skills, and

• analyze barriers and facilitators to implementing decision support in practice.

#### Performance feedback

Results of the decision quality scored transcripts of baseline simulated calls will be presented and discussed at the workshop. Participants will also be provided with evaluation tools based on the Decision Support Analysis Tool (DSAT) to self appraise their own and workshop peers' quality of decision support during the case studies and role play activities. As well, the facilitator will provide ongoing feedback from case studies and role plays during the workshop. The DSAT self-appraisal tool has been used to train nurses and medical residents in self-appraisal at the University of Ottawa, the Dartmouth Hitchcock Medical Center, and the US Health Dialogue call center.

#### Education outreach

Two weeks following the workshop intervention group participants will be scheduled for a personal academic detailing session with the workshop facilitator. Based on social marketing approaches educational outreach provides a focused opportunity to personalize learning and behavioral objectives, provide unbiased descriptions of research evidence and opinion leaders' positions, augment educational materials and reinforce positive behavior [63]. Academic detailing using brief, face-to-face interactions has shown promise for modifying physician and dentists practices [64,65] although one study reported initial resistance to the approach [66] and it had no effect as a single intervention [67].

The detailer will provide individualized information and resources, reinforce decision support behaviors, and help participants to identify opportunities for incorporating decision support behaviors into their practice. The one-to-one session will be scheduled at a mutually agreed time, will be conducted by telephone and should last about 15–30 minutes.

### Outcome Measures

#### Primary Outcome Phase 2

*Quality of Decision Support Skills *will be measured with DSAT modelled on the ODSF and Ivey's Problem Solving Model [68]. The DSAT, with total possible score of 12, assesses the quality of decision support and consists of subscales measuring decision support and communication in a practitioner/patient dyad. The tool demonstrated adequate inter-rater reliability for scoring on both decision support skills (75%, kappa = 0.58) and communication skills (76%, Kappa = 0.68) when it was tested in physician/patient dyads (n = 34 dyads). Construct validity was demonstrated when the scores were correlated to measures of patient and physician satisfaction[56] The DSAT also discriminates between trained and untrained nurses [33].

#### Secondary Outcomes Phase 2

Measures include:

• a knowledge test regarding decision support concepts;

• self assessment of decision protocol utility and helpfulness;

• behavioral intention to integrate decision support into clinical practice; and

• acceptability and utility of intervention components in the experimental group.

### Analysis Plan

#### Primary Outcome Phase 2: Quality of nurses' decision support skills

1. Inter-rater reliability of DSAT scores; two raters, who are blind to group allocation, will independently score pre and post intervention simulated call audio tapes.

2. Primary analysis will be undertaken using a repeated measures ANOVA (baseline; post measures). For missing cases an 'intention to treat', approach will be used under the conservative assumption that no change would occur between pre and post testing. Additionally, the impact of missing cases on findings will be explored between groups to provide further direction for the analysis.

#### Secondary outcomes Phase 2

1. Descriptive measures (frequency; means; range) will describe participant characteristics and acceptability and utility of training intervention components.

2. Descriptive measures (frequency; means; range) of the TPB based survey eliciting behavioral intention to integrate decision support in practice and related attitudes, norms, and perceived control will be undertaken. Between group differences in intention to integrate decision support practices will be analyzed using a t test.

3. Data from qualitative open-ended questions using traditional content analysis techniques [69,70] with the TPB as an organizing framework will be undertaken. Thematic coding, followed by member checking to ensure trustworthiness of final themes, will be undertaken.

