**Methods/Design:**

The efficacy of a brief education intervention will be assessed in a two-phase study. In phase one a focused needs assessment will be conducted with key informants. Phase two is a randomized control trial where clinicians will be randomly allocated to an intervention or control group. The intervention, informed by the needs assessment, knowledge transfer best practices and the ODSF, comprises an online tutorial; an interactive skills building workshop; a decision support protocol; performance feedback, and educational outreach. Participants will be assessed: a) at baseline (quality of decision support); b) after the tutorial (knowledge); and c) four weeks after the other interventions (quality of decision support, intention to incorporate decision support into practice and perceived usefulness of intervention components). Between group differences in the primary outcome (quality of decision support scores) will be analyzed using ANOVA.

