#### Sample Size

The estimated sample size for the Phase 2 study is based on a test for differences in mean scores of decision support quality and knowledge in the intervention versus the control group. An effect size of .70 requires n = 32/group, when alpha error = 0.05 and beta error = 0.20 [55]. This effect size is conservative in that a previous study (17) reported larger effect sizes which required only 18–20 per group.

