##### Phase 2 Intervention

Consenting practitioners will be randomly allocated to one of two groups. A computer generated randomization list for concealed allocation will be used. To avoid disparate sample sizes permuted blocks will be used. Participants will be allocated by an external statistician, who has no connection to the study team, immediately after collection of baseline data.

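### The primary repeated measures ANOVA amounts to a change-score test, which is valid but less precise than ANCOVA on the baseline score already collected, and is not the test used to size the trial

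*Protocol article*

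**What the plan says.** Three places in the protocol article describe the primary comparison.

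- **Analysis Plan, primary outcome:** "Primary analysis will be undertaken using a repeated measures ANOVA (baseline; post measures". The effect that tests the hypothesis is not named. A missing post score is handled by assuming no change from baseline.
- **Abstract, Methods/Design:** "Between group differences in the primary outcome (quality of decision support scores) will be analyzed using ANOVA".
- **Sample Size:** the calculation "is based on a test for differences in mean scores of decision support quality and knowledge in the intervention versus the control group", with the result "An effect size of .70 requires n = 32/group, when alpha error = 0.05 and beta error = 0.20". It uses no baseline score and no pre-post correlation.

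The baseline DSAT score comes from one simulated call and is collected before allocation (Phase 2 Intervention; Baseline measures of both groups). The post score comes from another call and "will be assessed with a different simulated patient scenario using the same methodology as the baseline assessment". The baseline score is nowhere used as a covariate.

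**The concern.** The analysis section and the sample size section use different tests. The sized test ignores baseline. The planned test subtracts baseline in full, whatever its correlation with the post score. When that correlation is low, subtracting baseline adds more noise than it removes. ANCOVA estimates how much of the baseline to subtract, so in large samples it is at least as precise as either alternative.

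The article makes a larger trial conditional on this result (Abstract, Discussion; Discussion). A real effect missed because of a less precise test would therefore have consequences, and the better test needs only data that the trial already collects.

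**Working it through.** **Inputs.** From Sample Size: standardised effect d = 0.70, n = 32 per group, alpha 0.05, beta 0.20. From Phase 2 Intervention: two randomised groups. Assumed, because the article does not state them: a two-sided test, d in units of the post-score SD, and the values of r and of k = SD_pre/SD_post.

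**Step 1: the stated figure.** The normal approximation gives n = 2 × (1.960 + 0.842)² / 0.70² = 32.04 per group. Strict rounding up gives 33. At n = 32, power is 80.0% by the normal approximation and 78.7% by the noncentral t. A one-sided test would need only 26. The stated 32 is therefore a two-sided comparison of two means without baseline.

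**Step 2: the variances.** Set the post-score SD to 1.

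- Planned group-by-time test (change score): variance 1 + k² − 2rk. With equal SDs (k = 1) this is 2(1 − r).
- ANCOVA on baseline: residual variance 1 − r², with one degree of freedom lost.
- With k = 1 the ratio ANCOVA/change is (1 − r²) / [2(1 − r)] = (1 + r)/2, which is below 1 for every r below 1.
- The change score is noisier than the post score alone when 1 + k² − 2rk > 1, that is r < k/2 = SD_pre/(2 × SD_post). With equal SDs the threshold is 0.5.

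**Step 3: power at 32 per group, equal SDs (noncentral t).** The effective d is 0.70/√[2(1 − r)] for the planned test and 0.70/√(1 − r²) for ANCOVA.

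| r | Effective d, planned | Power, planned | Effective d, ANCOVA | Power, ANCOVA |
|---|---|---|---|---|
| 0 | 0.495 | 50% | 0.700 | 79% |
| 0.2 | 0.553 | 59% | 0.714 | 80% |
| 0.3 | 0.592 | 64% | 0.734 | 82% |
| 0.5 | 0.700 | 79% | 0.808 | 89% |
| 0.7 | 0.904 | 95% | 0.980 | 97% |

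A simulation of 4,000 trials at each of r = 0.2, 0.3, 0.5 and 0.7 agreed: 58%, 65%, 77% and 94% for the change score, and 79%, 82%, 88% and 97% for ANCOVA. By the normal approximation, 80% power at r = 0.3 needs 45 per group with the planned test and 30 with ANCOVA.

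**Step 4: baseline less variable than post, k = 0.6 (an illustration).** The change variance is 1 + 0.36 − 1.2r.

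| r | Change variance | Power, planned | Power, ANCOVA |
|---|---|---|---|
| 0.2 | 1.12 | 74% | 80% |
| 0.3 | 1.00 | 79% | 82% |
| 0.4 | 0.88 | 84% | 85% |

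The threshold is now r = 0.3, and the loss is much smaller than with equal SDs.

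**The case against.** The strongest reply is that no shortfall has been shown. It depends on r and on the SDs, and the article gives neither. At r = 0.5 with equal SDs the planned test matches the sized one, and above that it does better. Design Limitations calls many of the skills novel, so baseline scores may be compressed, and Step 4 shows that this shrinks the loss. All of this stands, and it is why the result is given as a range.

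Sample Size also calls 0.70 conservative, because larger effects in a previous study needed only 18–20 per group. Those numbers imply d of about 0.91 to 0.96. At such effects the planned test, with 32 per group and equal SDs, has 81–85% power at r = 0.2 and 86–89% at r = 0.3. That margin is real, but it does not make the change score the better test.

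The article does not say which SD standardises 0.70. If it is the SD of change, the planned test has its stated power. The reference to mean scores favours the score SD without settling the matter.

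Finally, the interaction test is unbiased and holds its type I error under randomisation, and the Background presents the work as exploratory. Both points are correct, and they limit this to a matter of efficiency.

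**Conclusion.** The planned primary test is valid but less precise than ANCOVA on the same data, and it is not the test behind the 32 per group. With equal SDs and d = 0.70 in score-SD units, ANCOVA gains about 21 percentage points of power at r = 0.2, 18 at r = 0.3, 10 at r = 0.5 and 3 at r = 0.7. A modest r is plausible, because each score is a single call and the two calls use different scenarios, but nothing in the article establishes it.

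A reader might infer three stronger points that the article does not support.

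- **That the trial is underpowered or its sample size is wrong.** The 32 per group is correct for the test it describes, and power drops below that test only if r < SD_pre/(2 × SD_post).
- **That the abstract makes the group effect averaged over both times the primary test.** Its sentence is a condensed description. The null hypothesis under Aims of the study and the no-change rule for missing cases both point to change, hence to the interaction.
- **That the DSAT reliability figures, such as "decision support skills (75%, kappa = 0.58", show a low r.** They are agreement between raters for two skill areas, measured in physician/patient dyads. They say nothing direct about the correlation between two calls by the same participant.

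**What to change.** In the Analysis Plan, replace the repeated measures sentence with wording such as: *The primary analysis is an ANCOVA of the post-intervention DSAT total score on allocated group, with baseline DSAT total score as covariate. The adjusted mean difference is reported with its 95% confidence interval and two-sided p value.* Change from baseline can still be shown descriptively.

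In the abstract, name the same analysis. If the no-change rule for missing cases is kept, add that the missing post score is set to the participant's baseline score before the ANCOVA is fitted.

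The 32 per group can stand. Under ANCOVA it gives about 79–80% power or more for any r of zero or above. One clause in Sample Size should say that it was sized without baseline adjustment.

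The cost is a few sentences, with no new data, participants or procedures. If the repeated measures ANOVA is kept, the article should name the group-by-time interaction as the primary test and restate the sample size with an assumed r and SDs.

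### Filling a missing post score with the baseline score is labelled intention to treat and conservative; the first label is misapplied and the second is not assured

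*Protocol article*

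**What the plan says.** The Analysis Plan (Primary Outcome Phase 2) names the test: "Primary analysis will be undertaken using a repeated measures ANOVA (baseline; post measures". It then fixes the handling of missing scores: "For missing cases an 'intention to treat', approach will be used" "under the conservative assumption that no change would occur between pre and post testing". The section Phase 2 Intervention has allocation follow the baseline assessment, so every randomised participant has a baseline score. The missing score is therefore the post score, and the rule is baseline carried forward in both arms.

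The Analysis Plan adds that "the impact of missing cases on findings will be explored between groups to provide further direction for the analysis". It names no method for this.

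Under Post measures of both groups, the second call is made "with a different simulated patient scenario using the same methodology as the baseline assessment". Design Limitations says that participants know they are being assessed, and that skills are not expected to improve without the workshop and later practice.

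**The concern.** Two labels are attached to the rule, and neither fits.

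- **Intention to treat** defines the analysis set: everyone, in the arm to which they were randomised. It does not say what value replaces a score that was never observed. A plan can be fully intention to treat with or without this rule.
- **Conservative** would be right if the rule could only move the estimate towards no effect. It sets the change to zero for everyone without a post score, including trained participants who merely missed the second call. If scores in both arms also move between the two calls, because the second scenario is harder or easier or because of practice, the filled zeros remove different amounts of that movement from each arm whenever the missing shares differ.

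At stake are the size of the only primary result, which the Discussion uses to decide on a larger trial, and in some configurations the false-positive rate.

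**Working it through.** **Inputs from the protocol.** Sample Size: "An effect size of .70 requires n = 32/group", "when alpha error = 0.05 and beta error = 0.20", "based on a test for differences in mean scores of decision support quality and knowledge in the intervention versus the control group". Analysis Plan: two groups, two times. The group-by-time test in that design is the two-sample t test on change scores.

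**Inputs that are assumed.** The document gives no missing rate, common shift or pre-post correlation r. The values below are illustrations.

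**Step 1: the plan's own figure.** n per group = 2(1.960 + 0.842)²/0.70² = 32.04, which matches the stated 32 (two-sided). Power at 32 per group is 0.7996 by the normal approximation and 0.787 by the exact t calculation.

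**Step 2: what the rule estimates.** Work in SD units, with missingness unrelated to the scores within each arm. The mean change after filling is (1-pI)(D+T) in the intervention arm and (1-pC)T in the control arm.

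- Estimate = (1-pI)(D+T) - (1-pC)T
- Bias = estimate - D = -pI*D - (pI-pC)*T

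The first term always shrinks a positive effect. The second can have either sign, and it is zero if T = 0 or pI = pC.

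**Step 3: numbers put in.**

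| D | T | Missing, intervention/control | Estimate |
|---|---|---|---|
| 0.70 | 0 | 20%/10% | 0.80 × 0.70 = 0.56 |
| 0.70 | +0.5 | 10%/30% | 0.90 × 1.20 - 0.70 × 0.5 = 0.73 |
| 0 | -0.5 | 25%/5% | -(0.20)(-0.5) = +0.10 |
| 0 | +0.5 | 5%/25% | -(-0.20)(0.5) = +0.10 |
| 0 | +0.5 | 25%/5% | -(0.20)(0.5) = -0.10 |
| 0 | 0 | any | 0 |

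The second row shows that even dilution is not universal.

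**Step 4: power and error rates by simulation.** 32 per arm, t test on change scores.

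- *D = 0.70, T = 0, 20%/10% missing.* With the rule, power is 51% (r = 0.3) and 65% (r = 0.5). The same test on observed cases gives 56% and 72%. The cost is about 6 points; the rounded differences are 5 and 7.
- *D = 0.70, T = 0, 20% missing in both arms, r = 0.5.* 0.68 with the rule and 0.69 on observed cases, so almost no power is lost. The harm here is the biased estimate.
- *D = 0, T = -0.5, 25%/5% missing.* False significance in favour of the intervention is about 6%, against a nominal 2.5%.
- *D = 0 with T = 0, or with equal missingness.* Total type I error stays at about 5%.

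Under the same missingness, analysing observed cases gives about 0.70 for a true 0.70, about 0 under the null, and about 5% type I error.

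**The case against.** **Dilution is what the authors meant by conservative.** Shrinking towards no effect is the usual sense of the word, and the protocol declares it openly in a study that calls itself exploratory. This stands as a reading of intent. It does not make the direction certain, and it does not make the diluted figure a good estimate of the effect.

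**The protocol expects no gain without the workshop.** That points to T near zero, where no false effect arises. This narrows the point: a common shift is possible, not established. The expectation concerns improvement in untrained participants. It does not cover a second scenario that is harder or easier, and it gives no reason to assign zero change to trained participants whose post score is missing.

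**Burden may favour the claim.** Only the intervention arm has the tutorial, workshop and outreach call, so a reader may expect more missing scores there. If scores rise at the second call, the bias then runs against the intervention, as the word conservative implies. A false benefit under that dropout pattern needs scores to fall. At a milder 20%/10% with a fall of 0.5 SD, the bias is only +0.05 and the two-sided error about 5%.

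**Two stronger readings are not supported.**

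- A reader might set the 51-65% power under the rule against the 74-83% obtainable with ANCOVA on observed scores and blame the rule for the whole gap. Most of that gap comes from changing the test. The rule accounts for about 6 points.
- A reader might take the closing phrase about further direction as permission to replace the primary analysis once results are seen. The sentence describes a between-group check of missingness. It is loosely worded, but it does not say that.

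**Conclusion.** The point holds in limited form and should be fixed, though it is not critical. Intention to treat is the wrong name for an imputation rule, and conservative is a property the rule does not guarantee. Its usual effect is to understate a real benefit, by the intervention arm's missing share when T = 0 (0.70 to 0.56 at 20%). The power cost is modest at unequal missingness and close to nil at equal missingness.

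A reader might infer that the rule will manufacture a benefit. The document does not support that. It takes a common shift and unequal missingness together, in one of two pairings: controls missing more while scores rise, or the intervention arm missing more while scores fall. In the illustrated case the false estimate is +0.10 SD, with about 6% false significance in favour instead of 2.5%.

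The bias formula assumes missingness unrelated to the scores within each arm. The formula is exact under that condition, but the sizes rest on missing rates, shifts and correlations that are not in the protocol.

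**What to change.** In the Analysis Plan for the primary outcome:

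1. Make the primary estimate a likelihood-based mixed model of baseline and post scores, or ANCOVA with multiple imputation by arm. Include all participants as randomised, under a stated missing-at-random assumption.
2. Use intention to treat only for the analysis set.
3. Keep no change from baseline as a named sensitivity analysis, beside a tipping-point analysis that shifts the missing scores by arm.
4. Delete the word conservative.
5. State that the exploration of missing cases is a sensitivity analysis and does not alter the primary analysis.

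The cost is analysis wording only, with no change to design, data collection or sample size. The downside is reliance on missing-at-random, which the tipping-point analysis probes, and possibly slightly wider intervals.
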